## Background

Born prematurely and its consequences cause major impact on society and health indicators of population. According to the 2012 “Born Too Soon: The Global Action Report on Preterm Birth” of the World Health Organization, Brazil is ranked 10th among the countries with the highest number of preterm live births and 16th in deaths due to complications of prematurity [1]. The data from 2012 indicate that approximately 3 million babies are born in Brazil each year, 350,000 of whom are born with less than 37 weeks of gestation, and prematurity index is higher in the last three years, including preterm very low birth weight infants (gestational age less than 32 weeks and birth weight less than 1500 g). More than half of the preterm infants with birth weight less than 1500 g and gestational age GA of 23–33 weeks born in public university centers of Brazilian Neonatal Research Network died or were discharged with severe pulmonary, neurological or ophthalmological complications [1, 2].

Assistance in the delivery room with effective resuscitation is important for high risk infants and among the survivors is imperatives a continuous follow up clinic program. Follow up program is a continuous of neonatal and perinatal care and should provide conditions to monitor growth, development and common morbidities with a multidisciplinary team able to fully assess the child and the caregivers, parents, all family and school [3, 4]. According Cochrane Review there is a great deal of heterogeneity between studies due to the variety of early intervention programs and gestational ages included in these studies [5].

Despite of those evidences, the role of the family applying those programs at home is not well studied especially in social deprived environments. It is possible that a care process modified by households is beneficial for neurodevelopment outcome, in both; cognitive and motor skills.

Any early intervention for high risk preterm infant must focus in the parents-infant relationship, environment and behavior attitudes in order to reduce stress among parents of prematurely born children and improves neurovelopment outcome their children during childhood [6]. So, our main hypotheses is that a continuous global early stimulation done by parents at home for very preterm infants is better than the traditional one, and it can be offered to many very preterm infants even in poor environments.

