### Outcomes

Primary outcome: a global neurodevelopment evaluation will be obtained at 12 to 18 months corrected age for all patients to compare the effect of early systematic intervention independently of formal enriched environments in motor and cognitive aspects. The infants will be evaluated in relation to their motor, and cognitive neurodevelopment using AIMS and Bayley III scales between 12 and 18 months corrected age [14–16].

AIMS (Alberta motor infant scale): a blinded physiotherapist will evaluate the children of both groups between 12 and 18 months with Alberta Infant Motor (AIMS) scale in all eligible patients. The evaluation will be conducted in the presence of parents or caregivers in a safe surface with room for the child move around during the evaluation. The examiner will interact with the child to encourage response, but physical facilitation of movement should be avoided. During the evaluation, they are punctuated behaviors more or less mature within the motor repertoire of the child in each position (supine, prone, sitting and standing). This repertoire is called “motor” window. All items priced within the window motor and the window motor to the previous items are scored. The evaluation of the end, the child will receive a score based on the sum of the items scored on each posture, called raw score. This score will be observed in a standardized chart to find the baby development percentile according to the chronological age or corrected. Percentiles instrument standards are: 5%, 10%, 25%, 50%, 75%. According to this percentile baby’s development can be classified into three categories: normal or typical (percentile> 25%), suspicious (percentile> 5% and ≤ 25%), abnormal or atypical (percentil≤5%) [14].

BSDI-III: *Bayley scales of infant and toddler development third edition*: The Bayley Scales of Infant and Toddler Development, Third Edition, will be used for assessment of neurodevelopment at 12 and 18 months’ corrected age. The scales will be administered at the hospital clinic, on the same day of each follow-up visit, by a psychologist who was blinded to group allocation. Cognitive, motor, and language development will be considered normal if higher than 89; below average if 80 to 89; borderline if 70 to 79; and extremely low if less or equal 69. Examine all the facets of a young child’s development according manual [15].

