**Fig. 1 Fig1:**
[figure not shown]
Study flow chart. The flow chart of enrolment, allocation, intervention and assessment. *Intervention Group has ten additional appointments for systematic orientation for a continuous global simulation at home and ten home visits

Sample size: the sample size was calculated on the basis of the results of many studies that assessed improvement of motor and mental development or cognitive or language acquisitions. All these studies obtained minimum scores 20% higher after early intervention. For a 5% level of significance and a statistical power of 80%, a sample size of 84 patients will be required to detect a 3-point between-group difference in development scores [20, 24–26]. The allocation of the subjects will be perfomed until the complete calculated sample size based on the number of premature infants who survive until hospital discharge. A number of 20% (number 16) will be added, considering possible loss or death during the follow-up. Total sample size will be 100 preterm infants.

Recruitment: strategies for achieving adequate participant enrolment to reach target sample size will be: to establish a link between the research team and mother and father of each of the subjects included, regardless of the group allocated since randomization. Weekly meetings are performed during NICU stay.

A telephone number is available twenty-four for all questions after discharge and during the follow up. This mobile phone stays each day with a researcher’s member on call to resolve doubts with clarity and security. A prior scheduling of home visits and office appointments is done continuously during the recruitment and assessment according the objectives.

Assignment of interventions: Monitoring the progress of this research is fundamental for assuring that all activities will be achieving stated milestones. The selection of adequate method for generating the randomization sequence is important for result measurements. We have used the research randomizer program available at www.randomizer.org [23].

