Growth velocity will be registered in the reference curves, using the two computers with an appropriate statistical program for nutritional assessment (ANTHRO). There are two nutritionists to perform the growth evaluations in the exact moments in each group (blinded to which group the child was previously allocated). In the Intervention Group there will be a Nutritionist that will make home visits with the team to reinforce breastfeeding practices. The research team is using a check list during the home visits to the Intervention Group; home visits should be done at least two more researchers.

Statistical methods: All analyses will be performed in the PASW Statistics® for Windows, Version 18.0 software environment (Chicago, IL: SPSS Inc. Released 2009). Qualitative variables will be expressed as absolute and relative frequencies. Pearson chi-square test will be employed to determine the association between categorical variables, with adjusted residuals in case of statistical significance.

Symmetrically distributed continuous variables will be described as means and standard deviations, while asymmetrical distributed categorical variables being described as medians and interquartile ranges. Fisher’s exact test for comparison of categorical variables and Student’s t or the Mann–Whitney tests for comparisons of symmetrically distributed quantitative variables and asymmetrically distributed variables, respectively will be used. Subgroup and any additional analyses will be performed to adjust for social status, maternal age and some preterm’s neonatal conditions associated with poor neurodevelopment outcome.

Monitoring: There are five researchers to monitor data without competing interest. All researchers are independent from sponsor. Data are continuously monitored during the study. The teaching activities and educational programs for the families will be the focus of our research group throughout the study and if some adverse events occur, will be reported. Previous published study showed that the intervention during NICU stay is safe; the 10 additional appointments and 10 home visits will check the intervention safety [23].

Table 2 summarizes the project framework regarding specific objectives, outcomes and period of activities.

**Table 2 Tab2:** Project Framework: specific objectives, outcomes and period of activities

Specific Objectives	Outcomes	Period acticvities
Objective 1:		

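### The general rule for categorical variables ignores the order of the AIMS and Bayley classes; if the three- or four-level classes are compared under it, that comparison gives up roughly 10 to 20 points of power

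*Protocol article*

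**What the plan says.** All references are to the protocol article.

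- **Outcomes, Bayley III.** Four graded classes: "Cognitive, motor, and language development will be considered normal if higher than 89; below average if 80 to 89; borderline if 70 to 79", with extremely low at 69 or less.
- **Outcomes, AIMS.** The "baby’s development can be classified into three categories: normal or typical" (above the 25th percentile), suspicious (above the 5th, up to the 25th) and abnormal (5th or lower). The same section also yields an AIMS raw score and percentile, and numeric Bayley scores.
- **Statistical methods.** For categorical data, "Pearson chi-square test will be employed to determine the association between categorical variables, with adjusted residuals in case of statistical significance". Fisher's exact test is also named for categorical variables. Student's t and Mann-Whitney are named for symmetrically distributed quantitative variables and asymmetrically distributed variables. Neither AIMS nor Bayley is mentioned here.
- **Background.** The hypothesis is directional: "a continuous global early stimulation done by parents at home for very preterm infants is better than the traditional one".
- **Sample size.** At 5% significance and 80% power, "a sample size of 84 patients will be required" and the aim is "to detect a 3-point between-group difference in development scores". No SD is given.
- **Table 2, Objective 3.** The categorical neurodevelopment results listed are counts of children who are normal on Bayley III and normal on AIMS. Both are binary.

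**The concern.** On a 2×3 or 2×4 table, Pearson's chi-square (2 or 3 degrees of freedom) and Fisher's exact test give the same result however the columns are shuffled. They ask whether the arms differ in any way. The hypothesis is that children in the intervention arm move towards better classes. A test that spreads its sensitivity over patterns that are neither better nor worse has less power for that shift, and its rejection does not by itself show improvement.

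The adjusted residuals make this worse for an ordered outcome. They single out cells after a significant result (an excess of borderline children, for example) instead of estimating one overall shift.

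The article gives both scores and classes for its primary scales and does not say that the score is the only primary comparison. A class comparison could therefore carry weight in the report.

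**Working it through.** **1. The plan's own figure.** Taking 84 as 42 per arm, two-sided 5%, 80% power:

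d = (1.960 + 0.842) × √(2/42) = 0.611 SD.

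A 3-point difference is 0.611 SD only if SD = 3/0.611 = 4.91. The article states no SD, so 84 can be back-solved but not reproduced. At this d the normal approximation gives 80% and the exact t-test 79.1%. This is a power for scores.

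**2. Cost of extra degrees of freedom, analytically.** The non-centrality for 80% power on 1 df is (1.960 + 0.842)² = 7.849. The same signal gives:

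- 1 df: 80.0%
- 2 df (three classes): 70.9%, a loss of 9.1 points
- 3 df (four classes): 64.5%, a loss of 15.5 points

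**3. Simulation.** A normal score is shifted by d = 0.611 and cut into classes; 42 per arm, 20,000 trials per row. The article gives no class proportions, so those in the control arm are assumptions.

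| Control classes, worst to best (%) | Pearson | Mann-Whitney | Gain | Normal v not normal, 1 df |
|---|---|---|---|---|
| AIMS 5/20/75 | 33.2 | 45.9 | 12.7 | 46.4 |
| AIMS 10/20/70 | 39.0 | 50.4 | 11.4 | 50.1 |
| AIMS 20/30/50 | 52.8 | 63.1 | 10.3 | 61.1 |
| AIMS thirds | 58.2 | 68.4 | 10.2 | 63.5 |
| Bayley 5/10/25/60 | 38.1 | 57.8 | 19.7 | 55.3 |
| Bayley 10/20/30/40 | 49.0 | 67.5 | 18.5 | 64.0 |
| Bayley quarters | 54.5 | 71.4 | 16.9 | 59.1 |

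The linear-by-linear trend test is within 1 point of Mann-Whitney in every row. With no true difference, Pearson rejects in 4.0 to 5.1% of trials and Mann-Whitney in 4.7 to 5.1%, so the gain is not bought with type I error. With 50 per arm the gains are 10 to 13 points (AIMS) and 16 to 20 (Bayley).

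**4. Splitting the shortfall from the score test (79.1%).**

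- AIMS 10/20/70: 79.1 − 50.4 = 28.7 points from cutting the score into classes; 50.4 − 39.0 = 11.4 from ignoring order.
- Bayley 10/20/30/40: 79.1 − 67.5 = 11.6 from cutting; 67.5 − 49.0 = 18.5 from ignoring order.

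Cutting costs more in five of the seven rows; ignoring order costs more in the last two Bayley rows. No ordered test in the table reaches 80%.

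**5. Sensitivity to the assumed effect, with the Bayley cut-offs fixed and 42 per arm.**

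- SD 15 (assumed) and a 9.17-point shift (0.611 SD), control mean 85 to 100: gain 17 to 20 points.
- SD 15 and 3 points (0.2 SD): the t-test has 14.8% power, Pearson 5.5 to 8.9%, the ordered test 9.9 to 12.8%; gain about 4 points.
- SD 4.9 and 3 points: gain 12 points at control mean 85, 8 at 90 and under 1 at 95 or 100, where nearly all children fall in one or two classes.

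**The case against.** **The rule is generic.** It names neither scale and must also serve baseline and neonatal variables. The classes may be only interpretive bands beside the scores. This stands: that the three- and four-level classes will be tested by Pearson's chi-square is something a reader might infer, but the article does not say it. On the other side, in a 2×2 table all four adjusted residuals have the same absolute value, so mentioning them makes sense only for larger tables. The AIMS and Bayley classes are multi-level outcomes to which the rule, as worded, applies.

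**The categorical outcomes actually listed are binary.** This stands in full. For the normal/not-normal counts in Table 2, chi-square has 1 df, is equivalent to the two-sided test of two proportions, ignores no order, and shows direction through the two percentages.

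**The 80% is untouched.** A reader might conclude that the stated test pulls the trial below its planned power. The documents do not support that. The sample size concerns a difference in scores, which the same section sends to Student's t or Mann-Whitney.

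**A rank test may already be allowed.** The section describes some categorical variables by medians and interquartile ranges, which presupposes order, and names Mann-Whitney for asymmetrically distributed variables. That wording may be a slip for continuous variables. It makes the text ambiguous but does not assign an ordered test to the classes.

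**An unseen analysis plan may settle it.** It may. But the point rests on a rule the article does state, not on missing detail.

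**Conclusion.** The point holds in a limited form. The only tests clearly assigned to categorical variables ignore order, while the article defines ordered classes on both primary scales. Any comparison of the three- or four-level classes under that rule loses about 10 to 13 points of power for AIMS and 17 to 20 for Bayley, relative to an ordered test on the same data.

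This size rests on assumed control distributions, a normal underlying score, and a uniform shift of 0.61 SD. That shift equals the planned 3 points only at an SD near 4.9, which the article does not state. With a smaller standardised effect, or when nearly all children fall in one or two classes, the loss is smaller.

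Three stronger conclusions do not follow: that the planned 80% is reduced, that an ordered test would restore the class comparison to 80%, or that the binary counts in Table 2 are wrongly tested. The point is worth acting on because the remedy costs almost nothing.

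**What to change.** In the Statistical methods paragraph:

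1. Compare the three AIMS classes and the four Bayley classes between arms with a linear-by-linear trend test or a Mann-Whitney test on the ordered classes; name one.
2. Report an ordered effect estimate, such as a common odds ratio or the probability of a better class, with a 95% confidence interval.
3. Drop adjusted residuals for these outcomes.
4. Keep Pearson or Fisher for nominal variables and for the normal/not-normal counts of Table 2.
5. State that the 80% power refers to the comparison of scores and that class comparisons are supportive.

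Cost: a wording change, with no new data, visits or patients, best made while the analysts are still blinded. The downside is slightly less sensitivity to non-ordered patterns, which the hypothesis does not concern.

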Ophthalmologist	Evaluation of Retinopathy of Prematurity (ROP), visual acuity, strabismus
Ear, nose and throat doctor	Evaluation and management of hearing problems
Nutritionist	Management of growth failure
Speech Therapist	Speech problems and swallowing problems
Nurse	Immunization and Hygiene control

During the appointments, feeding orientations, weight gain, general health/illness and infections are recorded. A 24 h dietary recall is administered at each visit to assess feeding routines, use of formula, breast milk, and family food preferences. Routinely feeding orientations have been offered according their needs (exclusive breastfeeding or mixed feeding or infant formula; nutritional requirements according their corrected age). Recurrent admissions during the first year of life, anthropometric parameters (weight, head circumference, body mass index, and length at 6, 12 and 18 months of corrected age (z scores plotted on WHO growth charts), and results of routine tests performed at 1 year of corrected of age are systematically recorded.

Patients will have their motor neurodevelopment evaluated by AIMS (Alberta Infant Motor Scale at 6 and 12 moths of CA) and forwarding to specialized professionals according to their necessity. The scale was translated and adapted to the Portuguese language, being quick and easy to application. The reliability and reproducibility showed satisfactory values [14]. Applications of the Bayley Scales, cognition, language and motor (BSDI- III, Bayley Scale Development Index, version III), by qualified and trained professional will be performed at 12 months CA for all infants [15].

The examiner is able to distinguish, by means of comprehensive and standardized protocols for neurological development, developmental scales and tests between the normal biological variation and the deviant development. The clinical approach has the great advantage of being easily repeated, obtaining developmental trajectories that can lead to neurological disorders being suspected in both arms [16] .

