AIMS and Bayley Scales are recommended to use together and in different ages because false positives are common and therefore it is beneficial to follow-up children at high risk of motor impairment at more than one time point, or to use a combination of assessment tools [8].

Secondary outcome: We have evaluated parental stress and parental infant bonding at hospital discharge in all preterm infants included in the study and survival in the neonatal period.

PARENTAL BONDING INSTRUMENT (PBI) had been applied by a professional blind to the group to which the child belongs. These questionnaires are to be used for research purposes only. PBI is a self-administered Likert scale (0 to 3) instrument, with 25 questions related to father and mother, in which subjects answer how similar those behaviors were to their parents’ behavior until the age of 16 years. The instrument measures two constructs: the first one is affection, which is more consistent and clearly bipolar (affection, heat, availability, care, sensitiveness versus coldness and rejection); the second construct is control or protection (control, intrusion versus encouragement of autonomy) [20].

Emotional availability scales –EAS: this scale will be used to assess both groups at the end of the study. The EAS consists of six scales; four scales assess adult emotions and behavior related to sensitivity, structuring, non-intrusiveness, and non-hostility. The other two scales are related to child behavior. Child responsiveness to the caregiver assess the child interactions with the adult; and child involvement with the caregiver scale assesses the behaviors regarding to child invitations to caregiver to join her in the play and the interaction talks with the caregiver. The scales scores are obtained by scores measured in each dimension using a Likert-type continuous scale with scores between 1 and 7.

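### Bayley-III is planned at 12 and 18 months, but the named tests take one score per infant; a mixed model would protect an 18-month comparison against unequal loss, at a modest gain

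*Protocol article*

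**What the plan says.** **Bayley-III.** Under Outcomes, the scales "will be used for assessment of neurodevelopment at 12 and 18 months" corrected age, on the day of each follow-up visit, by a blinded psychologist. The follow-up text for the conventional group in Methods instead says that Bayley testing "by qualified and trained professional will be performed at 12 months CA for all infants". The primary outcome itself is described as an evaluation in a window of 12 to 18 months.

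**AIMS.** The follow-up text schedules "AIMS (Alberta Infant Motor Scale at 6 and 12 moths of CA) and forwarding to specialized professionals according to their necessity". The outcome assessment is a different one: "a blinded physiotherapist will evaluate the children of both groups between 12 and 18 months with Alberta Infant Motor (AIMS) scale".

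**Analysis.** For quantitative variables the Statistical methods paragraph names Student's t and Mann–Whitney: "tests for comparisons of symmetrically distributed quantitative variables and asymmetrically distributed variables, respectively will be used". For categorical variables it names chi-square and Fisher. It adds unspecified further analyses to adjust for social status, maternal age and neonatal conditions. No method that links two scores from one infant is named.

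**Loss.** The Sample size paragraph adds 16 infants to 84, "considering possible loss or death during the follow-up", for a total of 100. Table 2, Objective 2, lists home visits among the means of keeping loss low. Only the intervention group has the ten home visits and ten extra appointments.

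**The concern.** All four named tests need one value per infant. With Bayley scored at two ages, the trial must either choose one age or use a method that takes both. Some text points to the later age. Table 2, Objective 3, places the follow-up evaluations after the ten sessions and home visits, and the ninth and tenth appointments fall between 13 and 18 months. A 12-month score therefore comes before the programme is complete.

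If the 18-month score is compared by t-test, an infant with a 12-month score but no 18-month score contributes nothing. Under purely random loss this costs some precision. It causes bias if infants with low earlier scores are lost more often and this happens mainly in one arm. The design makes unequal loss plausible, because one arm receives home visits, which the plan itself regards as a means of retention, and the other does not. The earlier score that could correct for this would already be on file.

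**Working it through.** **1. The plan's own figures.** The 84 infants cannot be reproduced, because no SD is given for the 3-point difference. Solving back for 42 per arm, two-sided 5% and 80% power:

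SD = 3 × √(42/2) / (1.960 + 0.842) = 4.91 points, so the planned effect is 3/4.91 = 0.61 SD.

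The loss allowance is 84 + 16 = 100. That is 16% of those enrolled, although the text calls it 20% (20% of 84 is 16.8). A true 20% loss from 100 would leave 80.

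**2. Assumptions not in the documents.** The 18-month score is the one compared. There are 50 infants per arm. The correlation ρ between the 12- and 18-month scores is 0.5 to 0.7, extended to 0.8 for power. The true 18-month effect is 0.62 SD, close to the 0.61 SD above.

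**3. Random loss between the visits.** Suppose all n infants in an arm have a 12-month score and a share d lack the 18-month score.

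- t-test on observed 18-month scores: variance of the arm mean = σ² / [n(1 − d)]
- Repeated-measures model: σ² × [(1 − ρ²) / (n(1 − d)) + ρ² / n]
- Ratio of the second to the first: 1 − dρ²

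For d = 0.16:

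| ρ | Ratio | Variance reduction |
|---|---|---|
| 0.5 | 1 − 0.16 × 0.25 = 0.960 | 4.0% |
| 0.6 | 1 − 0.16 × 0.36 = 0.942 | 5.8% |
| 0.7 | 1 − 0.16 × 0.49 = 0.922 | 7.8% |

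A simulation of 6,000 trials per setting gave ratios of 0.97, 0.95 and 0.92.

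Power for 3 points at SD 4.91:

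| Loss | t-test | Model, ρ = 0.5 | ρ = 0.7 | ρ = 0.8 |
|---|---|---|---|---|
| 16% | 80.0% | 81.6% | 83.1% | 84.1% |
| 20% | 78.1% | 80.1% | 82.1% | 83.4% |

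If half of the 16% is lost before 12 months, those infants have no earlier Bayley score. The ratio becomes 1 − ρ² × 0.08/0.92, a reduction of 2.2% (ρ = 0.5) to 4.3% (ρ = 0.7). With d = 0 the ratio is 1, so there is no gain.

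**4. Selective loss in the control arm.** Assume that 22% of controls are lost, more often when the 12-month score is low, and 8% of intervention infants are lost at random. If the lost controls average m SD below all controls at 12 months, the observed control mean at 18 months is too high by

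ρ × m × 0.22/0.78 = 0.282 × ρ × m (in SD).

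With m = 0.7:

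- ρ = 0.5: 0.099 SD
- ρ = 0.6: 0.118 SD
- ρ = 0.7: 0.138 SD

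This is about 0.10 to 0.14 SD. The arm difference shrinks by that amount. Simulation of the same loss pattern on an SD of 15 and a true difference of 9.3 points gave biases of −1.42, −1.65 and −1.93 points (0.095, 0.110 and 0.129 SD), which corresponds to m of about 0.65 to 0.67. The repeated-measures estimate was off by 0.01, 0.05 and 0.07 points.

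As a share of the assumed effect, the range runs from 1.42/9.3 = 15% to 0.14/0.62 = 23%. On the SD of 4.91 implied by the sample size, 0.10 to 0.14 SD is 0.49 to 0.69 points, or 16% to 23% of 3 points.

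**The case against.** **The repeated schedule is not firmly established.** The follow-up text gives Bayley at 12 months only, and the primary outcome is described as a window. This stands. If Bayley is done once, the point falls away for Bayley, so the schedule must be reconciled first.

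**Discarding of infants is an inference.** A reader might conclude that earlier scores are wasted and that infants lost before the last visit are excluded. The article does not say so. It does not name the analysed visit, and with a 12 to 18 month window an infant seen only at 12 months could count. The loss of infants is therefore conditional on comparing 18-month scores. The alternative is no cleaner, because letting 12-month scores stand in would mix ages and degrees of exposure to the programme.

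**AIMS is not clearly repeated.** A reader might set "Alberta Infant Motor Scale at 6 and 12 moths of CA" beside the outcome AIMS and treat them as one series. The former sits in the clinic follow-up text and is tied to referral. Nothing says it is a blinded outcome.

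**The stated rationale does not demand repeated analysis.** The article says that "it is beneficial to follow-up children at high risk of motor impairment at more than one time point", but the same sentence offers a combination of tools as an alternative, and the trial uses two scales. It concerns false positives in individual children, not how arm means are compared.

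**A single-age comparison is valid, and an analysis plan not shown may add a model.** Both are true. The point rests on the tests that the article does name, which cannot use both of the scores it plans.

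**The size is easily overstated.** Setting 1.4 to 1.9 points, computed at SD 15, against the 3-point target suggests a bias of half to two thirds of the effect. That mixes scales: at SD 15 a 3-point difference would need 786 infants, whereas 84 implies SD 4.91. The loss pattern is also assumed, and it places all loss between the two visits. The bias shown runs toward no effect, so this scenario gives no ground for fearing a false positive.

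**Conclusion.** The point holds in a limited form. The article plans two Bayley scores in one place and names only tests that take one value per infant. If 18-month scores are compared, infants seen at 12 but not at 18 months are left out, and a mixed model handles this better with data already planned.

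The benefit is modest. Variance falls by about 4% to 8% under 16% random loss between the visits, by less if part of the loss comes before 12 months, and by essentially nothing without loss. Under the assumed selective loss of controls, the model removes a bias of about 0.10 to 0.14 SD toward no effect, 15% to 23% of the assumed effect.

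These figures rest on the assumed correlation, effect, loss rates and dependence of loss on the earlier score, none of which the documents give. The article does not show that earlier scores will be discarded, nor that AIMS is affected in the same way.

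**What to change.** 1. Reconcile the Outcomes section with the follow-up text on when Bayley-III is done, and name the age of the main comparison.
2. Where Bayley is scored at both ages, analyse the continuous scores with a linear mixed model: arm, visit, arm by visit, and unstructured within-infant covariance. Include every infant with at least one score.
3. Report the arm difference at the later age as the result. Do not average the two visits, since the earlier one precedes the last sessions. Keep the t-test as a supporting analysis.
4. Bring AIMS into such a model only if the clinic assessments at 6 and 12 months are confirmed to be comparable, blinded outcome data.
5. Keep the counts of infants with normal Bayley and AIMS results (Table 2, Objective 3) as separate categorical analyses.

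The cost is about one paragraph of wording and slightly more analysis work, with no new visits, data or infants. The model assumes that loss depends only on observed data. This is a weaker assumption than the complete-case comparison makes, but it is still an assumption and should be stated.
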